## Study methods

This is a multi-centre, randomised, double-blinded, placebo-controlled trial of melatonin versus placebo to decrease the rate of delirium in ICU. A total of 850 ICU patients have been randomised on a 1:1 ratio to receive either melatonin or a placebo. Study participants were administered an oral dose of melatonin 4 mg enterally or placebo once daily at 21:00hs. for up to 14 days or until discharge from the ICU. Participants were monitored twice daily for symptoms of delirium. Additionally, data is being collected on the duration and severity of delirium, sleep quality, hospital and ICU length of stay (LOS), duration of mechanical ventilation, and mortality.

Patients were randomised according to a computer-generated randomisation list, stratified by site, with standard block sizes of 6. Variable block sizes were considered unlikely to provide additional benefit, as the study drug and placebo have the same appearance and all clinical staff are blinded, thus maintaining allocation concealment. The randomisation list has been maintained by the University of Western Australia Centre for Applied Statistics.

The patients, investigators, ICU doctors, and nurses looking after patients enrolled in the study are blinded to the treatment that the patients are receiving. Only the University of Western Australia Centre for Applied Statistics, the compounding pharmacy, and the independent Data Safety Monitoring Committee (DSMC) (should they need to, in order to investigate an adverse event) have had access to the treatment allocation list.

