Based on the sample size calculations, with an alpha value of 0.05 and a power of 80%, a total of 850 patients have been recruited to the study, with 425 patients in each arm. Estimates of sample size were made based on the percentage of delirium-free assessments (the primary outcome) and, secondarily, the ICU LOS. LOS was chosen in addition to the percentage of delirium-free assessments as a significant relationship between delirium and LOS has been observed. Delirium assessment is by its nature subjective and the investigators wished to also allow the study to be powered to detect a reduction of LOS of 1 day (as an objective patient-orientated outcome). An audit of 100 patients across the two primary sites was used to provide preliminary data to guide sample size calculations where an average of 54% of assessments were deemed delirium free (standard deviation of ± 45%). The research group is interested in being able to detect a 10% increase in the percentage of delirium-free assessments. This would require a sample size calculation of 319 per group. Adjustment for non-parametric data (15%) increases this to 367 per group. It is expected that up to 10% of patients recruited in the study will not be assessable for delirium at any point during the study. To account for this, and missing data/loss to follow-up, the sample size was increased by 15% to 423 patients per group (total rounded to 850).

To detect a change in LOS of 1 day, using a sample size calculation for a gamma distribution, 387 patients per group would be required. The greater number of 850 was selected to have enough power to answer both questions. The formula used to calculate sample size was that described by Wand and Chow in 2007 [27].

The framework of the study is of superiority of melatonin over placebo for the prevention of delirium. Superiority analyses will be two-sided and considered statistically significant at the 5% level.

The DSMC is comprised of an independent intensivist, an epidemiologist, and a statistician independent of the trial statistician. The independent DSMC will review all serious adverse events and perform an interim analysis after 400 patients using the Haybittle-Peto stopping rule. The Haybittle-Peto stopping rule states that if an interim analysis shows a probability of equal to or less than 0.001 that a difference as extreme or more between the treatments is found, given that the null hypothesis is true, then the trial should be stopped early [28].

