**Fig. 1 Fig1:**
[figure not shown]
Statistical analysis plan flowchart version 1

Baseline characteristics including age, gender, severity scores, source of admission, and diagnosis will be presented as a table and summarised.

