Finally, an analysis that looks at whether the individual reported a positive delirium assessment during their stay will be undertaken by comparing proportions between the groups through a logistic regression analysis controlling for variables including age, gender and length of stay.

The secondary outcomes to be analysed include (1) severity and duration of delirium, (2) sleep quality, (3) ICU and hospital length of stay;,(4) duration of mechanical ventilation, (5) mortality, and (6) economic analysis. Each secondary outcome will be adjusted for the same covariates as mentioned before: age, gender, delirium subtype, diagnostic category, and Pre-Deliric score.

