### ICU and hospital length of stay

Initial comparisons between the two groups for ICU and hospital length of stay will be compared using Student’s *t* test. Supporting analysis will also be carried out using Poisson regression, accounting for previously described covariates. Length of stay will be analysed in particular with the aforementioned subgroups.

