### Mortality

Mortality (time to death) will be analysed using Kaplan-Meier curves and Cox proportional hazard models, both unadjusted and adjusting for previously described covariates. Individuals who did not experience an event (death) will be censored at the end of the follow-up period of the study. Individuals withdrawn from the study early or lost to follow-up will be censored at the date of withdrawal or the last contact visit respectively. Results will be presented using hazard ratios and 95% confidence intervals for relative comparisons between the groups and absolute risk and differences will be estimated at both 28 and 90 days.

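### Baseline severity scores are tabulated but left out of the fixed covariates for mortality and length of stay, at a modest cost in power

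*SAP article*

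**What the plan says.** Under Trial population, in the text below Fig. 1, the SAP article states: "Baseline characteristics including age, gender, severity scores, source of admission, and diagnosis will be presented as a table and summarised". Severity scores are therefore expected to be at hand.

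Under Analysis, the covariates age, gender, delirium subtype, diagnostic category and Pre-Deliric score are named for the Poisson model of positive delirium assessments. The same five are then applied to all secondary outcomes: "Each secondary outcome will be adjusted for the same covariates as mentioned before: age, gender, delirium subtype, diagnostic category, and Pre-Deliric score". No severity score is named.

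- **Mortality:** "Kaplan-Meier curves and Cox proportional hazard models, both unadjusted and adjusting for previously described covariates".
- **Length of stay (ICU and hospital):** "Initial comparisons between the two groups for ICU and hospital length of stay will be compared using Student’s *t* test". A supporting Poisson regression uses the covariates already described.
- **Duration of mechanical ventilation:** the examples given are age, gender, admission type and diagnosis type, so the article does vary the covariates for at least one outcome.

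Under Study methods, patients were "randomised on a 1:1 ratio", with the list "stratified by site, with standard block sizes of 6". Severity is not a stratum. The same section also uses a 1-day change in ICU LOS, needing 387 per group, to support the total of 850.

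**The concern.** The covariate list is built around the risk of delirium. For time to death, and plausibly for LOS, general severity of illness is a natural prognostic factor. The trial plans to tabulate it, yet it enters neither the design nor any named model for these outcomes.

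Two things are at stake. In a Cox model, an omitted prognostic covariate moves the treatment hazard ratio toward 1, with some loss of power. For LOS, which helped to set the sample size, the first comparison makes no use of baseline information, and the adjusted supporting model lacks the severity score. Adding severity after unblinding would be a data-driven choice, so the time to fix it is before.

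**Working it through.** **1. The plan's own figures.** The inputs from Study methods are "with an alpha value of 0.05 and a power of 80" per cent, with two-sided tests ("Superiority analyses will be two-sided and considered statistically significant at the 5% level"). For the primary outcome (difference 10 points, SD 45), n = 2 × (1.96 + 0.8416)² × 45² / 10² = 317.9, or 318 per group. The t-based solution is 318.8, giving the stated 319. Then 319 × 1.15 = 366.9 (367) and 367 × 1.15 = 422.05 (423). These reproduce, and this point disputes none of them. The 387 per group for LOS cannot be reproduced, because the mean and shape of the gamma distribution are not given.

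**2. Length of stay.** Back-calculating by normal approximation from 387 per group, 1 day and 80% power:

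SD = 1 / [(1.96 + 0.8416) × √(2/387)] = 1 / 0.2014 = 4.97 days.

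At 425 per group the standard error is 4.97 × √(2/425) = 0.341 day, so power = Φ(1/0.341 − 1.96) = 83.5%.

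If the covariates of a linear model explain a share R² of the variance, the standard error is multiplied by √(1 − R²). The article gives no R², so the range is assumed:

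| R² (assumed) | Standard error, days | Power at 425 per group |
|---|---|---|
| 0 (t test) | 0.341 | 83.5% |
| 0.05 | 0.332 | 85.4% |
| 0.10 | 0.323 | 87.2% |
| 0.16 | 0.312 | 89.3% |

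This is the gain of an adjusted linear comparison over the t test, for all its covariates together. Severity alone accounts for only part of it.

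**3. Mortality.** The article gives no event rate, target hazard ratio or severity association, so all of these are assumed. The setting is n = 850, 1:1, exponential times censored at 90 days and a two-sided 5% Wald test. Severity is a standard normal covariate. The comparator model already holds a covariate correlated 0.5 with severity, standing in for the Pre-Deliric score. With 1,500 simulated trials per row:

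| Control-arm 90-day mortality | True HR | Log-HR per SD of severity | Power without severity | Power with severity |
|---|---|---|---|---|
| 15% | 0.65 | 0.5 | 60.5% | 60.7% |
| 15% | 0.65 | 0.8 | 55.5% | 58.3% |
| 15% | 0.70 | 0.5 | 45.2% | 46.3% |
| 15% | 0.70 | 0.8 | 41.9% | 44.6% |
| 25% | 0.65 | 0.5 | 81.4% | 82.7% |
| 25% | 0.65 | 0.8 | 76.7% | 81.9% |
| 25% | 0.70 | 0.5 | 66.3% | 68.5% |
| 25% | 0.70 | 0.8 | 62.4% | 67.5% |

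The gain is 0-2 points at log-HR 0.5 and 3-5 points at 0.8. Another simulation over the same range of inputs gave about 3-7 points. Both amount to a few points, and the size depends mainly on how strongly severity predicts death.

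The mechanism shows in the row with 25% mortality, HR 0.65 and log-HR 0.8. The mean log-HR is −0.41 without severity and −0.43 with it (true value log 0.65 = −0.43), while the standard error is 0.152 in both models.

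**The case against.** The strongest reply is that nothing here is wrong in itself. Five prespecified covariates beside an unadjusted analysis is a valid plan. The trial is not sized for mortality, and LOS power of about 83.5% already exceeds the 80% target. Age, diagnostic category and a Pre-Deliric score from the first 24 hours may carry much of the severity information. The article names neither the severity instrument nor its timing, and it refers to additional files that are not shown. The sickest patients may die early and so have short stays, which makes the link between severity and LOS uncertain.

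Most of this stands, and it limits the weight of the point. It does not remove it: as written, the list keeps a baseline prognostic score out of every mortality and LOS model.

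Stronger readings that a reader might infer are not supported:

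- **That the hazard ratio loses precision.** Its standard error is unchanged; the effect is attenuation.
- **That the covariate list weakens the LOS t test.** That test uses no covariates, so lengthening the list alone would not alter it.
- **That possible chance imbalance in severity is a flaw.** The type I error of a randomised comparison already covers it, and at 425 per arm its 95% limits are only 1.96 × √(2/425) = 0.134 SD.
- **That mortality is the main safety outcome.** The article lists it as one of six secondary outcomes and assesses harms through adverse events.

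**Conclusion.** The point holds as an improvement of minor to moderate weight. The omission leaves the mortality hazard ratio somewhat closer to 1 than a severity-adjusted one and costs a few power points: close to none if severity is a moderate predictor, and at most about 7 within the assumed range. For LOS, a covariate-adjusted linear comparison would raise power from about 83.5% to 85-89%.

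All of these sizes rest on assumptions. The LOS standard deviation is back-calculated by normal approximation from a gamma-based sample size, and R², mortality, hazard ratio and the severity association are not in the article. The primary analysis and the sample size are unaffected.

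**What to change.** Before unblinding:

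1. Under Analysis, name one baseline severity score, with its instrument and timing, and add it as a continuous covariate for mortality and for ICU and hospital LOS.
2. Under Mortality, state in advance whether the unadjusted or the adjusted hazard ratio leads.
3. Under ICU and hospital length of stay, add a covariate-adjusted difference in days from a linear model with robust standard errors beside the t test, and state in advance which leads.

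The cost is SAP wording and one extra covariate. The article's multiple-imputation provision for variables other than the outcome already covers missing scores. The small downside is overlap with the Pre-Deliric score: this blurs the separate covariate coefficients rather than the treatment effect, and it means the gain may be modest. The article reports that follow-up was still under way and allocation still blinded, so the change could be made without knowledge of results.

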### Severity and duration of delirium

All analyses, with the exception of ‘Delirium and Coma Free Days’, will use either a linear mixed model approach or generalised linear mixed model approach. Both of these will include a random individual effect to account for the repeated nature of the data and an appropriate correlation structure. Estimated differences between the groups and 95% confidence intervals will be provided throughout. The following analyses will be undertaken:
CAM-S: Score: CAM-S scores range from 0 (no delirium) to 7 (severe delirium). Linear mixed models will be used to compare CAM-S score as a response between the two treatment groups for individuals who have tested positive using CAM-ICU.Delirium and Coma-Free Days: Poisson regression will be used to compare the count of delirium and coma-free days between the treatment groups using an offset of number of days in ICU.Anti-psychotics or sedation: The use of anti-psychotics or sedations will be recorded as a binary outcome labelled ‘used’ or ‘not used’ for each day during the study period. Generalised linear mixed models with logit link will be used to compare the two treatment groups with respect to the binary outcome.Physical restraint: Each day during the study period, the use of physical restraints will be recorded as a binary outcome labelled having been ‘used’ or ‘not used’. Generalised linear mixed models with logit link will be used to compare the use of restraints between the two treatment groups with respect to the binary outcome.Participation with physiotherapy and mobilisation: Ability of participate in physiotherapy and mobilisation sessions will be assessed as a binary outcome labelled ‘yes’ or ‘no’. Generalised linear mixed models with logit link will be used to compare the use of the two treatment groups with respect to the binary outcome.Patient removal of lines: Each day during the study period, it will be recorded as whether or not the patient has attempted to or successfully removed their lines (binary outcome labelled ‘yes’ or ‘no’). Generalised linear mixed models with logit link will be used to compare the used to compare the use of the two treatment groups with respect to the binary outcome.Type of delirium: At each assessment, patients with delirium will be classified as having either hyperactive, hypoactive, mixed delirium, or no delirium. Generalised linear mixed models for ordinal response will be used to compare the use of the two treatment groups with respect to the ordinal outcome.

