**Discussion:**

The SAP details the analyses that will be done to avoid bias coming from knowledge of the results in advance. This trial will determine whether prophylactic melatonin administered to intensive care unit patients helps decrease the rate and the severity of delirium.

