## Statistical principles

Differences will be considered statistically significant when *P* values are < 0.05, and 95% confidence intervals (95% CI) will be reported.

Adherence to protocol will be considered when patients have received all the required doses while in ICU and all the CAM-ICU assessments. This will be presented with descriptive statistics as a percentage and numerator and denominator. Protocol deviation is defined as lack of compliance with study drug administration or lack of assessment with CAM-ICU. All protocol deviations will be collated and presented in the results as descriptive statistics. All analyses will be conducted on both an intention-to-treat (ITT) and per-protocol (PP) basis. The ITT sample is defined as all randomised subjects including those who are lost to follow-up or have missing data. If the patient does not receive the assigned intervention post-randomisation, the patient will still be included in the ITT sample and analysed according to assigned treatment group.

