## Analysis

Primary and secondary outcomes will be analysed as described below. Where appropriate, analysis of primary and secondary outcomes will be analysed by a number of predetermined subgroups. These subgroups will include (1) percentage of delirium-free assessments by age: less than 65 or more than 65 years of age; (2) percentage of delirium-free assessments by gender; (3) percentage of delirium-free assessments by delirium subgroup at baseline: hyperactive, hypoactive, and mixed, as well as no delirium; (4) percentage of delirium-free assessments by diagnostic category (respiratory, cardiovascular, gastrointestinal, toxicological, neurological, metabolic, sepsis, trauma, traumatic brain injury); and (5) percentage of delirium-free assessments by > 50% risk or < 50% risk as per Pre-Deliric Score (calculated from first 24 h of ICU admission). Multiplicity adjustments will not be made.

For the primary outcome of percentage of delirium-free episodes, patients will be assessed for delirium twice a day for 14 days or until they are discharged from ICU, whichever occurs first. The CAM-ICU tool will be used to assess delirium, with a result recorded as either ‘positive’ or ‘negative’ for delirium. The assessment will be carried out by trained ICU medical or nursing staff. The percentage of delirium-free assessments will be calculated for each participant. The percentage of delirium-free assessments for participants in each group will then be compared using Student’s *t* test. It is assumed that the data will be normally distributed. If the distribution of the data is not normally distributed, alternative approaches will be considered; however, the initial plan is robust to deviations from normality with this sample size. Supporting analysis will use linear regression making adjustments for baseline covariates.

A secondary analysis will look at the rates of delirium in each group. The number of times an individual is reported as being positive for delirium and the total number of assessments will be examined by a comparison of rates. In addition, a Poisson regression will be used with the number of positive delirium assessments reported and offset the total number of assessments. Baseline characteristics will be included as covariates in the model. The covariates will include age, gender, delirium subtype, diagnostic category, and Pre-Deliric score.

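### Delirium severity (CAM-S) is compared only in CAM-ICU-positive patients, a set largely defined after randomisation by the event melatonin is meant to prevent; the resulting bias can run either way

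*SAP article*

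**What the plan says.** Under Severity and duration of delirium, linear mixed models will "compare CAM-S score as a response between the two treatment groups for individuals who have tested positive using CAM-ICU". The same section gives the scale: "CAM-S scores range from 0 (no delirium) to 7 (severe delirium". On the mixed models it adds: "Both of these will include a random individual effect to account for the repeated nature of the data and an appropriate correlation structure". No CAM-S analysis in all patients is stated, and CAM-S is the only severity score analysed.

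Four other statements bear on this:

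- Study methods: "The framework of the study is of superiority of melatonin over placebo for the prevention of delirium".
- Analysis, on when CAM-ICU status is determined: "patients will be assessed for delirium twice a day for 14 days or until they are discharged from ICU, whichever occurs first".
- Statistical principles: "All analyses will be conducted on both an intention-to-treat (ITT) and per-protocol (PP) basis", and "The ITT sample is defined as all randomised subjects including those who are lost to follow-up or have missing data".
- Abstract, Discussion: the trial will determine whether "prophylactic melatonin administered to intensive care unit patients helps decrease the rate and the severity of delirium".

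The Analysis section also adjusts every secondary outcome for age, gender, delirium subtype, diagnostic category and Pre-Deliric score.

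**The concern.** CAM-ICU status is observed during treatment and is what treatment is meant to change. If melatonin prevents some delirium, the positive patients in the melatonin arm are those in whom prevention failed. The positive patients in the placebo arm also include those whom melatonin would have spared. The two sets are then different kinds of patient, and a difference in mean CAM-S mixes any effect on severity with that difference in composition.

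The wording leaves open whether the model takes all assessments of an ever-positive patient or only the positive assessments. Both select after randomisation. Covariate adjustment repairs this only if the five listed variables capture everything that determines severity and differs between the selected groups.

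At stake is the severity half of the announced conclusion. The positives-only estimate could be read as harm, or as benefit, when it reflects only who entered the set.

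**Working it through.** The plan gives no CAM-S mean, SD or patient-level delirium incidence, so there is no CAM-S figure to reproduce. The 425 patients per arm come from Study methods. Every other input below is an assumption, shown over a range. Each illustration uses one score per patient without covariates, which is simpler than the planned model.

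**1. Selection with no patient made worse.** Let p_C and p_M be the proportions ever positive on placebo and melatonin. Let s_A be the mean score of patients who would be positive in either arm, the same in both arms. Let s_P be the mean score on placebo of those whom melatonin would spare.

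- Mean among placebo positives = [p_M × s_A + (p_C − p_M) × s_P] / p_C
- Mean among melatonin positives = s_A
- Positives-only difference (melatonin minus placebo) = (p_C − p_M)(s_A − s_P) / p_C
- All-patient difference, with 0 for no delirium = −(p_C − p_M) × s_P

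The sign of the positives-only difference depends only on whether the prevented cases would have been milder or more severe than the rest. With p_C = 0.50, p_M = 0.40 and s_A = 5:

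| s_P | Positives only | All patients |
|---|---|---|
| 6 | 0.10 × (−1) / 0.50 = −0.20 | −0.60 |
| 5 | 0.00 | −0.50 |
| 4 | 0.10 × 1 / 0.50 = +0.20 | −0.40 |
| 3 | 0.10 × 2 / 0.50 = +0.40 | −0.30 |

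Over incidence pairs from 30%/20% to 80%/70%, the positives-only difference is +0.12 to +0.67 when s_P is 4 or 3, and −0.33 to −0.12 when s_P is 6. The all-patient difference shows benefit throughout.

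**2. Chance of a misleading significant result.** Simulation of 4,000 trials with 425 per arm, 50% v 40%, and SD 1.5 assumed:

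- Prevented cases equally severe: 2.4% significant against melatonin, 2.4% in favour.
- Prevented cases 1 point milder: 25% against.
- Prevented cases 2 points milder: 68% against (62% with 60% v 50%).
- Prevented cases 1 point more severe: 25% in favour.

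**3. Uniform benefit.** Assume a latent severity with mean 2.5 on placebo, lowered by 0.6 for everyone on melatonin, rounded and limited to 0–7, and positive at 3 or more.

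- SD 2: positives 4.11 to 3.93, difference −0.18; all patients 2.59 to 2.08, difference −0.51.
- SD 2.5: positives 4.45 to 4.28, difference −0.18 before rounding the means; all patients 2.67 to 2.20, difference −0.47.

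Here the benefit is diluted and not reversed.

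**4. The extreme case.** Suppose 60% are ever positive on placebo (255 of 425), and melatonin prevents exactly the mildest sixth, leaving 50% (212). With normal severity, the mean of the remaining cases rises by φ(−0.967) / (5/6) = 0.30 SD, or 0.45 points if the SD is 1.5. With a common SD, z = 0.2998 / √(1/255 + 1/212) = 3.2. Truncation cuts the melatonin-arm SD to 0.79 of the placebo value, which gives z of about 3.6. If preventability is only correlated with severity, the shift scales with the correlation: 0.5 gives 0.15 SD (z about 1.7), 0.3 gives 0.09 SD (z about 1.0), and 0 gives none.

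**The case against.** A reader might infer that the analysis is biased against melatonin whenever prevention works. The document does not support that. Nothing in it says which cases melatonin would prevent, and the calculations show a bias of nil, against melatonin or in its favour, or a dilution. A significant false worsening needs a marked severity gap between prevented and remaining cases.

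A reader might also infer that a preventive benefit would be hidden, or that the trial could say nothing about delirium burden. Neither follows. The primary comparison, the Poisson and logistic analyses, delirium and coma-free days, and the type-of-delirium model (which has a no-delirium category) carry no stated positives-only restriction. CAM-S would be read beside them.

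Two further points stand. Baseline delirium is one of the subgroups, so some positive patients were delirious before treatment and were not selected by it; their share is unknown, and they weaken the bias. Adjustment for Pre-Deliric score and the other covariates could change its size.

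None of this turns the positives-only comparison into a randomised one. The other unrestricted analyses address occurrence, days, type or management, and none of them uses a severity score.

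**Conclusion.** The point holds as one about a single secondary analysis. The CAM-S set is largely post-randomisation, departs from the plan's own definition of intention to treat, and has no all-patient companion, although the scale has a value for no delirium. Selection alone could move the estimate by a few tenths of a CAM-S point in either direction. The size rests on assumed incidences and severities, and the significance rates also on the assumed SD. The shift of 0.30 SD is the extreme and not the expected case. That selection occurs if melatonin prevents any delirium follows from the text; its direction and size do not. By itself, the analysis cannot support a claim that melatonin lowers, or raises, the severity of delirium.

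**What to change.** Make the main CAM-S comparison in all randomised patients with at least one CAM-ICU assessment, analysed by assigned arm. Use the recorded CAM-S, or 0 where CAM-ICU is negative; leave assessments that could not be made as missing. Fit the planned mixed model or, given the many zeros, compare per-patient mean CAM-S with a linear model and robust standard errors. Report by arm the number never assessable. Study methods expects up to 10%, so this set also falls somewhat short of all randomised patients.

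Keep the positives-only model as a supportive analysis. State whether it uses all assessments of ever-positive patients or only positive ones. Label it as conditional on a post-randomisation event and not as evidence of a treatment effect on severity.

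The cost is a change of SAP wording, which can be made before unblinding (Trial status). There are real downsides. The score will contain many zeros, partly overlaps with the primary outcome, and answers a different question from severity among cases. The article does not say whether CAM-S was recorded at CAM-ICU-negative assessments; if it was not, the analysis rests on assigning 0 there, and the SAP should say so.

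### Type of delirium is analysed as ordinal although its subtypes have no evident rank and the plan states none, so the estimate depends on an unspecified order when treatment shifts the subtype mix

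*SAP article*

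**What the plan says.** The section on severity and duration of delirium in the SAP article lists seven analyses. The last is type of delirium: "At each assessment, patients with delirium will be classified as having either hyperactive, hypoactive, mixed delirium, or no delirium". The model is fixed in the next sentence: "Generalised linear mixed models for ordinal response will be used to compare the use of the two treatment groups", and the comparison is made "with respect to the ordinal outcome".

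The opening of that section applies to this analysis too. On the mixed models it says: "Both of these will include a random individual effect to account for the repeated nature of the data". On reporting it says: "Estimated differences between the groups and 95% confidence intervals will be provided throughout".

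No ranking of the four categories is given anywhere, and no nominal model is offered as an alternative. In the Analysis section the same categories appear as plain subgroups: "delirium subgroup at baseline: hyperactive, hypoactive, and mixed, as well as no delirium". Severity has a scale of its own, the CAM-S score from 0 to 7.

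**The concern.** An ordinal model needs categories that can be placed from less to more. Hyperactive, hypoactive and mixed delirium differ in kind. At most, none can be placed below any delirium. The plan does not present subtype as a grading of severity, because CAM-S does that work.

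Two things are at stake. First, the estimate is not pre-specified: whoever codes the variable chooses what is estimated, and sometimes its direction. Second, a move from one subtype to another, which an analysis of type exists to show, can largely cancel in a single ordinal coefficient.

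**Working it through.** The plan gives no figure for this outcome, so there is none to reproduce. The check is whether the ordinal estimate changes with the category order.

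**Inputs.** The none share is 54%, from the audit in the Study methods section ("an average of 54% of assessments were deemed delirium free"). The subtype split and the treatment shift are assumptions, because the document gives neither. Assessments per arm are set at 1000, and the random patient effect is left out; it would not remove the dependence on order.

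| | none | hypoactive | mixed | hyperactive |
|---|---|---|---|---|
| Placebo | 540 | 250 | 120 | 90 |
| Melatonin | 540 | 190 | 120 | 150 |

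**Model.** Proportional odds: logit P(Y ≤ k) = a_k − b × treatment, with OR = exp(b). With none lowest, OR above 1 means that melatonin shifts assessments towards later categories.

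**Odds ratio at each cut, by hand.**

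Order none-hypoactive-mixed-hyperactive:
- any delirium vs none: (460/540)/(460/540) = 1.00
- mixed or hyperactive vs the rest: (270/730)/(210/790) = 1.39
- hyperactive vs the rest: (150/850)/(90/910) = 1.78

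Order none-hyperactive-mixed-hypoactive:
- any delirium vs none: 1.00
- mixed or hypoactive vs the rest: (310/690)/(370/630) = 0.76
- hypoactive vs the rest: (190/810)/(250/750) = 0.70

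The common odds ratio is a compromise between the three cuts. By maximum likelihood it is **1.13** (z = +1.48) for the first order and **0.88** (z = −1.48) for the second. None is the lowest category in both, so the two figures have the same orientation and the change of side is real.

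**Order-free test of the same table.** Expected counts are the averages of the two arms. None and mixed contribute 0, hypoactive 2 × 30²/220 = 8.18, and hyperactive 2 × 30²/120 = 15.00. The total is **23.2 on 3 degrees of freedom**. Odds ratios against none are 190/250 = 0.76 for hypoactive, 120/120 = 1.00 for mixed and 150/90 = 1.67 for hyperactive.

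**How far clustering weakens that test.** The audit SD is 45%, so 0.45²/(0.54 × 0.46) = 0.82, a rough guide to the correlation of assessments within a patient. If subtype clusters to the same degree (an assumption), 425 patients per arm carry about 425/0.82, or about 520, independent assessments. The chi-square then scales to 23.2 × 0.52 = about 12, with P about 0.007.

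**Other assumed shares.** Placebo is none 54%, hypoactive 22%, mixed 14%, hyperactive 10%. None stays lowest and the three subtypes are permuted (six orders).

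| Assumed shift under melatonin | Range of ordinal OR | Order-free ORs vs none (hypoactive, mixed, hyperactive) |
|---|---|---|
| None unchanged; 10 points move from hypoactive to hyperactive | 0.81 to 1.24 | 0.55, 1.00, 2.00 |
| None 54% to 57%; hypoactive 22% to 9%; hyperactive 10% to 20% | 0.70 to 1.15 | 0.39, 0.95, 1.89 |
| None 54% to 64%; all subtypes cut in proportion | 0.68 in all six orders | 0.66, 0.66, 0.66 |

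The last row marks the limit of the concern: without a change in mix, the order of the subtypes does not matter.

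**The case against.** Several points on the other side stand.

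- **Order matters only under a condition.** With none at one end and a proportional fall in every subtype, the ordinal odds ratio is the same in all six orders. A reader might infer that the ordinal effect never has a meaning here; that goes too far.
- **The plan does not name a proportional-odds model or a common odds ratio.** It promises estimated differences with confidence intervals. A single cumulative odds ratio is the usual reading of an ordinal mixed model, but it is an inference.
- **The order of the words is not a coding rule.** A reader might infer that the plan places mixed next to none because the sentence lists them so. The text only lists categories. The fair criticism is that no order is fixed.
- **In the worked table no ordinal fit reaches the 5% level** (|z| is at most 1.48). A reader might infer that the trial could report a significant benefit or harm by choice of coding. The example does not show that. It shows a null-looking result of either sign while the subtype mix differs.
- **The weight is limited.** This is one of seven analyses under one of six secondary outcomes. The primary comparison, its supporting regression, the Poisson rate analysis and the ever-positive analysis do not use it.

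The core is not answered by any of this. The article names the outcome ordinal and commits to the ordinal model class, so this is not a detail lost by condensing a longer plan.

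**Conclusion.** The concern holds in a bounded form. The plan applies an ordinal model to categories whose three subtypes have no evident rank and for which it states none. When treatment shifts the subtype mix, the size and sign of the estimate depend on the order chosen: 1.13 against 0.88 in the worked table, and 0.70 to 1.15 or 0.81 to 1.24 under the other assumed shifts. When the mix is unchanged and none is at one end, nothing depends on the order of the subtypes.

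These figures rest on assumed subtype shares and shifts and on a model without the patient effect. They show that the dependence exists, not how large it will be in this trial. The chi-square of 23.2 should not be read with its nominal P value, because assessments within a patient are correlated.

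This should be fixed. It is not a threat to the trial's main conclusion, and a reader who infers that the primary result is affected finds no support in the plan.

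**What to change.** Replace the ordinal model with a multinomial (generalised logit) mixed model with no delirium as the reference category and a random patient effect. Report one odds ratio with its 95% confidence interval for each subtype. Separate logistic mixed models of each subtype against none are an acceptable approximation and use the logit mixed model already planned for restraint and line removal. They are not equivalent to the multinomial model, because each uses a different subset of assessments and its own random effect.

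The same edit should state which assessments enter. The present sentence classifies patients with delirium but allows none as a class, which leaves it open whether all assessments or only positive ones are analysed.

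The cost is a change of wording, with no new data. The article says that it was submitted before unblinding; a change made after unblinding should be labelled as such. The downside is three odds ratios instead of one, each less precise, above all for a rare subtype.
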